### Recruitment

This study will be conducted in the physical examination center of the Ningxia Hui Autonomous Region People’s Hospital. The number of NAFLD patients admitted to the physical examination center each year is enough to meet the sample size of this study. We will recruit participants through the WeChat public platform, posters, telephone visit, and the medical staff introductions.

For patients who wish to participate in the study, researchers will elaborate on the purpose, methods, possible risks, and rights of participants. If the patient is fully aware of the study and agrees to participate and meets the inclusion criteria, the investigator will ask the patient to sign an informed consent form.

### Participant retention and withdrawal

Once the participants are registered, the research team has the responsibility to achieve a low rate of loss to intervention. Before the start of the intervention, investigators will conduct education, detailing the duration of the intervention and possible adverse effects. During the intervention and follow-up period, the trained researchers will remind the subjects to take the capsules, fill in the capsule taking record form, ask if there is any uncomfortable, and give psychological support to participants.

All patients will be informed that they have the right to withdraw from the study at any time during the intervention and the Data Monitoring Committee (DMC) will discuss and analyze the reasons for dropouts with data collectors, which will be documented in a standardized proforma.

### Data collection, management, and confidentiality

Paper material of the original test data will be stored in a locked filing cabinet in the office of the Ningxia Medical University. All data will be fed into the computer by two researchers, and access passwords will be set to keep the data secure. Personal identifiable subject information related to the data will be replaced with anonymous numbers. In order to ensure the quality of data, an independent clinical research assistant will review the original data every month to check whether the data is correct and complete. The authors will follow the guidelines recommended by the International Committee of Medical Journal Editors (ICMJE).

### Data monitoring

A DMC, which is independent from the sponsor and any competing interests, will be set up at the same time the research project is identified refer to the DMC charter [21, 24]. The DMC includes a chief nutritionist, an endocrinologist, a chief nurse, and a statistical specialist who will serve as the DMC’s chair. During the implementation of the study, members of the DMC will review the original test data regularly, check the standardization of the study, ensure the completeness and accuracy of the data, and guarantee the credibility and dependability of the study results. If the study is found to be out of order, the DMC may make corrective recommendations or stop the test.

Any modifications of this protocol and changes to eligibility criteria or outcomes will be communicated with the DMC, project implementer, trial participants, and research ethics committee review board. In regular DMC meetings, they discuss project issues, modify the study design, and convey the protocol changes to the project implementer.

### Auditing

The trial funder will audit and review the source data to verify the accuracy, completeness, and safety of the data annually. What is more, the members of DMC and the responsible researchers will inspect the original documents, the fund utilizing, and the medical records of patients as well.

### Data analysis

All patients randomized should be included in the analysis and missing data will be handled using multiple imputation. The test data will be analyzed by a statistical expert using SPSS version 22.0 (Chicago, IL, USA). The statistical expert is not involved in the experiment and is only responsible for the analysis of the data. We will use descriptive statistical methods to measure demographics and baseline clinical features. The categorical variables will use the chi-square test or Fisher’s exact test for analysis and are reported as numbers and percentages. The numerical variables will be reported as mean±standard deviation or medians with interquartile ranges (IQR) comparing by Student’s *t* test or the Mann-Whitney *U* test. Ranked data will be analyzed using the rank-sum test. Follow-up data will be compared using the repeated measures analysis of variance (ANOVA). A multiple linear regression method was used to establish a linear equation of multiple linear regression to detect the interaction between the amount of physical activity and the efficacy of LBP supplements.

The alpha and beta diversity of the gut microbiota will be estimated by MOTHUR and QIIME at the OUT level, respectively. Sample cluster will be conducted by QIIME based on UPGMA. KEGG and COG functions will be predicted using the PICRUSt software. Barplot and heatmap of different classification levels will be plotted with T package v3.4.1 and R package “gplots”, respectively. Cases with missing values in the resulting parameters will be excluded from the analysis. All results are statistically significant with *P*<0.05.

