### Laboratory assessment and imaging

Laboratory investigations include liver enzymes (γ-glutamyltransferase (GGT), alanine aminotransferase (ALT), and aspartate aminotransferase (AST)); biochemical markers of lipogenesis such as triglycerides (TG), total cholesterol (TC), LDL-cholesterol, HDL-cholesterol, and free fatty acids (FFA); and inflammatory factors (IL-6, IL-1β, TNF-α, MCP-1). At baseline and 12 weeks, the blood sample will be collected for laboratory evaluation after a 12-h overnight fasting. Liver enzymes and lipid profiles (TG, TC, LDL-cholesterol, HDL-cholesterol) will be measured by an automatic biochemistry analyzer. The levels of FFA will be assayed using an FFA assay kit (Nanjing Jiancheng Bioengineering Institute, Nanjing, China). Gas chromatography-mass spectrometer (7890B-5977A GC/MSD, Agilent, USA) will be used for the short chain fatty acids (acetic acid, propanoic acid, butyric acid, isobutyric acid, N-valeric acid, isobutyric acid, caproic acid) analysis. The concentration of inflammatory factors will be determined by enzyme-linked immunosorbent assays (ELISA) kit (Elabscience Biotechnology Institute, China). All laboratory assessments will be performed in the same laboratory by using standard laboratory methods. At the beginning and the end of the intervention period, ultrasound examination of the abdomen will be performed on all patients, and the hepatic steatosis will be noted and graded.

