## Outcome measures

### Primary outcome measure

The primary outcome measure will be a significant ALT concentration relief after the intervention, which is assessed and recorded by the researchers according to the results of laboratory assessment.

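### Multiple imputation is planned, but ALT may be tested by a bare Mann-Whitney test, which gives one p-value per imputed set and nothing to pool; no single poolable ALT analysis is named

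*Protocol article*

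**What the plan says.** All the analysis statements below come from the Data analysis section of the protocol article.

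- Missing data: "All patients randomized should be included in the analysis and missing data will be handled using multiple imputation".
- Numerical variables: "The numerical variables will be reported as mean±standard deviation or medians with interquartile ranges (IQR) comparing by Student’s" t test or the Mann-Whitney test. No criterion for choosing is given.
- Ranked data: "Ranked data will be analyzed using the rank-sum test".
- Follow-up data: "Follow-up data will be compared using the repeated measures analysis of variance (ANOVA").
- Categorical variables: "The categorical variables will use the chi-square test or Fisher’s exact test for analysis".
- A multiple linear regression is also named, but for the interaction between physical activity and the supplement, not for the ALT comparison.

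The Primary outcome measure section makes ALT the primary outcome: "The primary outcome measure will be a significant ALT concentration relief after the intervention". Laboratory assessment and imaging gives its timing: "At baseline and 12 weeks, the blood sample will be collected for laboratory evaluation". The Sample size calculation section plans 25 patients per arm and allows for 20% drop-out. No sentence ties a particular test to ALT.

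**The concern.** Multiple imputation produces an answer only when an estimate and its standard error from each completed data set are combined. A Mann-Whitney or rank-sum test, run as a bare test, returns a p-value and no such pair. If ALT is judged skewed and sent to Mann-Whitney, the analyst holds several p-values for one primary comparison and the plan offers no model from which to get a single one.

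The missing share could be material. ALT is drawn only at baseline and week 12, so a patient who leaves before week 12 has no post-baseline ALT, and no intermediate ALT value informs the imputation. At stake is whether the primary comparison has one predefined verdict. Reading any one completed set also treats imputed values as observed, which makes the test too liberal.

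**Working it through.** The plan states no figure on this point, so there is none to reproduce. The check has four steps.

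**1. What pooling needs.** For m completed sets with estimates Q_j and variances U_j, Rubin's rules give

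- pooled estimate = mean of the Q_j;
- total variance T = mean(U_j) + (1 + 1/m) × B, where B is the variance of the Q_j between sets. With m = 5 the factor is 1 + 1/5 = 1.2.

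A bare p-value supplies neither Q_j nor U_j.

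**2. Which named tests supply them for ALT.**

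- *t test:* yes, the mean difference and its standard error.
- *Repeated measures ANOVA:* yes here. With two time points the group-by-time F is the squared t statistic of the change. A numerical check with 25 per arm gave F = 0.8877 and t² = 0.8877.
- *Mann-Whitney or rank-sum:* not as a bare test. It can be re-expressed as P(A<B), the probability that a value in one arm is below a value in the other, which has a standard error. The plan does not say so.
- *Chi-square or Fisher:* planned for categorical variables, so not relevant to ALT.

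**3. Size of the problem if Mann-Whitney is used without pooling.** Inputs from the protocol: 25 per arm; 20% drop-out, so 25 × 0.20 = 5 missing week-12 values per arm. Assumptions: normal data, baseline to week-12 correlation 0.6, 5 imputations, and a true effect of 0 or 0.82 SD. The 0.82 is an assumption because the protocol gives no SD. Set against its planned difference of 11.3 − 4.4 = 6.9, it would correspond to an SD of 6.9/0.82 = 8.4.

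| Result over the five sets | No effect | 0.82 SD |
|---|---|---|
| p-values on both sides of 0.05, first simulation (3,000 runs) | 15.0% | 27.3% |
| Same, second simulation with the same assumptions | about 15% | about 29% |
| One set read alone rejects | 8.6% and about 9% | not used |

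With 3,000 runs the Monte Carlo standard error on 15% is √(0.15 × 0.85/3000) = 0.65 percentage points.

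A third simulation used skewed (log-normal) ALT with log-SD 0.4 and correlation 0.7, both assumed. The effects were log reductions of 0.3 and 0.2.

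| Missing, imputations | Split, no effect | Split, with effect |
|---|---|---|
| 8%, 5 | 7% | 13% and 22% |
| 20%, 5 | 17% | 26% and 37% |
| 20%, 20 | 27% | 41% and 58% |

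More imputations without pooling make disagreement more frequent. When P(A<B) was pooled by Rubin's rules in the same simulation, there was one p-value and the type I error was 4.9% to 5.0%.

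**4. What a named regression gives.** Under the assumptions of step 3, a pooled regression of week-12 ALT on arm and baseline rejected in 4.7% of trials with no effect. Under 0.82 SD it had 83% power, against 72% for a pooled unadjusted t test. A separate run with 20 imputations gave 4.9% and 87%.

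The gain comes from baseline adjustment, not from pooling. At correlation 0.6 the outcome SD of 1 falls to √(1 − 0.36) = 0.80 with adjustment. A change score has SD √(2 − 1.2) = 0.89, so the gain over a t test on change would be smaller.

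**The case against.** The strongest reply is that the number of imputations and the pooling rule are details that a journal article leaves to the analysis plan, and that naming multiple imputation already implies pooling. This largely stands: the absent rule is not a finding by itself. What remains is that the protocol offers a bare rank test for a numerical primary outcome alongside imputation. An analysis plan would have to replace that test or convert it to another effect measure, not only fill in a detail.

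Second, the plan never assigns Mann-Whitney to ALT. Week-12 ALT is follow-up data, so repeated measures ANOVA is at least as natural a reading, and it pools. No ALT distribution is given, so skew is plausible but not documented. This stands and makes the point conditional.

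A reader might infer that every listed test except the t test is unusable after imputation, Fisher's included. The documents do not support that: step 2 shows that ANOVA pools with two ALT measurements, Mann-Whitney can be pooled through P(A<B), and Fisher's test is not for ALT.

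A reader might also infer that the primary result will be a set of conflicting p-values, or that the trial's type I error is 8.6%. The plan nowhere says that one imputed set is read or that several p-values are each held against 0.05. Those figures show what would follow from skipping the pooling step, not what is planned.

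Finally, a later sentence says: "Cases with missing values in the resulting parameters will be excluded from the analysis". It could be read as removing imputation altogether. It sits in the microbiota paragraph and its scope is not stated, so it does not settle how missing ALT is handled.

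**Conclusion.** The point holds as a conditional risk. The plan combines imputation of all randomized patients with a choice of tests for ALT, one of which gives nothing to pool as a bare test, and it does not say which test is primary. If Mann-Whitney is chosen and left unpooled, the imputed sets disagree about significance in about 15% of trials with no effect and 27% to 29% with a 0.82 SD effect. This assumes 20% missing, correlation 0.6 and 5 imputations. Across the skewed-data scenarios the range is 7% to 58%, driven by missingness, effect size and number of imputations. If the t test or the two-time-point ANOVA is used, the problem does not arise for ALT.

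The case for changing the text does not rest on that risk alone. A baseline-adjusted regression uses data already collected, pools without difficulty, and in the same setting had 83% power against 72% for the unadjusted t test.

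**What to change.** In the Data analysis section, name one primary ALT analysis: linear regression of week-12 ALT on arm and baseline ALT, fitted in each imputed data set, with the arm difference and its 95% CI pooled by Rubin's rules. If skew is expected, fix the log scale in advance rather than after looking at the data. Keep Mann-Whitney and rank-sum tests as sensitivity checks on observed data.

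The cost is analysis wording and a little more programming, with no new data. The downside is a model assumption on the ALT scale. On the log scale the effect becomes a ratio, while the sample size section works with absolute decreases, so the text should state how the two relate.

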### Intervention

According to the inclusion and exclusion criteria, all eligible patients will be introduced to the study. After investigators comprehensively review the inclusion and exclusion criteria and explain the purpose, benefits, and potential risks of the study, patients who agree to participate will be asked to sign an informed consent form (Additional file 2) and then be included in the study. At the baseline, participants will be randomized to allocate an intervention group or a control group. Patients assigned to the intervention group will receive an LBP supplementation capsule and those assigned to the control group will receive an identical appearance capsule containing maltodextrin as the placebo. In this study, the capsules are provided by Ningxia Wofu Bairui Biological Food Engineering Co., Ltd. The concentration of LBP supplementation capsules is 40% and the specification is 0.75 g per capsule. According to the recommended amount, patients will be instructed to take two capsules daily for 12 weeks and not to change their diet or daily physical activity. Follow-up assessments will be performed every 4 weeks at weeks 4, 8, and 12 after randomized allocation. The trained researcher will successively include patients until the target sample size is reached and the project manager will assign participants to interventions according to the randomization list. In general, both LBP supplementation and maltodextrin placebo are considered safe interventions without severe side effects for participants [20]. If any undesirable event occurs (bleeding, allergic and anaphylactic reactions, interactions with other prescriptions, etc.) or the participant requests to withdraw, the investigator can discern whether the trial should be continued. All reasons for terminating the trial will be recorded by the data collector.

There are many strategies that will be used to assess and improve patient compliance. Before administering the intervention, the baseline data of the participants will be generated and gathered. The investigator will detail the duration of the intervention, possible adverse effects, and provide capsules for a period of 4 weeks. The adherence will be assessed by checking the number of remaining capsules and a capsule intake questionnaire at each follow-up visit. At the same time, patients will obtain another set of capsules (every 4 weeks).

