### Sample size calculation

Based on the previous study results of supplementing synbiotics in NAFLD, this study took the significant reduction of ALT concentration as the main outcome indicator for sample size calculation. According to the research of Eslamparas et al. [23], it was found that the concentration of ALT decreased 11.3 and 4.4 in the intervention and control groups respectively. It aimed to determine an appropriate target sample size that would provide a 90% power (*β* = 0.10) for two-tailed testing with 5% type-1 error rate of the measure. Using the PASS 22.0 software, we calculated a minimum requirement of 42 patients for total. In practice, we decided to enroll a total of 50 participants (*n* = 25 per group), taking into account the 20% drop-out rate before the end of the study.

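### ALT, the primary outcome, is measured only at baseline and week 12, but no named comparison method adjusts for baseline ALT; ANCOVA would gain precision at no cost

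*Protocol article*

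**What the plan says.** - **Outcome.** The Primary outcome measure section reads "The primary outcome measure will be a significant ALT concentration relief after the intervention". It does not say whether relief means change from baseline or the level at week 12.
- **Timing.** The Laboratory assessment and imaging section, which covers liver enzymes, states "At baseline and 12 weeks, the blood sample will be collected for laboratory evaluation after a 12-h overnight fasting". The Intervention section adds visits, "Follow-up assessments will be performed every 4 weeks at weeks 4, 8, and 12 after randomized allocation", but no blood draw is assigned to weeks 4 and 8. Each patient therefore has one ALT value before treatment and one after.
- **Methods.** The Data analysis section states "The numerical variables will be reported as mean±standard deviation or medians with interquartile ranges (IQR) comparing by" Student's t or Mann-Whitney U, and then "Follow-up data will be compared using the repeated measures analysis of variance (ANOVA". The only regression named is one "to detect the interaction between the amount of physical activity and the efficacy of LBP supplements". No test is tied to ALT by name, and adjustment for baseline ALT is not mentioned.
- **Sample size.** The Sample size calculation section relies on an earlier synbiotic study in which "it was found that the concentration of ALT decreased 11.3 and 4.4 in the intervention and control groups respectively". From this, at 90% power and two-sided 5%, "we calculated a minimum requirement of 42 patients for total". Fifty are to be enrolled to allow for 20% drop-out. No SD is given.

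**The concern.** With a single post-treatment value, the natural analysis compares week-12 ALT between arms given baseline ALT. Each named option falls short of that:

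- A t or Mann-Whitney test on final values makes no use of baseline.
- The same test on change uses baseline, but fixes its coefficient at one instead of estimating it.
- Repeated-measures ANOVA on two time points adds nothing to the change-score test through its group-by-time term. Its group main effect averages in the pre-treatment value.

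With 25 per arm, baseline ALT may differ by chance, and no planned comparison corrects for this by regression. At stake are power and an estimate that depends less on such imbalance. The validity of the significance test is not at stake.

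**Working it through.** **Inputs**
- Difference in mean ALT decrease: 11.3 - 4.4 = 6.9 (Sample size calculation).
- Power 90%, two-sided 5%, 42 in total, so 21 per arm (same section).
- Completers: 25 x (1 - 0.20) = 20 per arm (same section).
- SD: not stated.
- Correlation r between baseline and week-12 ALT: not stated. Assumed 0.5 and 0.7, with 0.3 to 0.9 as a wider range.
- Equal ALT variance at both visits: assumed first, then relaxed.

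**Step 1. The plan's own figure.** Without an SD, 42 cannot be reproduced; it can only be solved backwards. A two-sample t calculation needs 21 per arm for SDs of 6.56 to 6.72, and the normal approximation for 6.74 to 6.89. At SD 6.73 the t-test with 21 per arm has 90.0% power. I use 6.73 and read it as the SD of change, because the planning figures are decreases.

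**Step 2. Variances.** Let S be the SD of change and s the SD of ALT at one visit.
- Final value: s = S / sqrt(2(1 - r)).
- ANCOVA residual SD: s x sqrt(1 - r²) = S x sqrt((1 + r)/2).
- ANCOVA variance relative to change: (1 + r)/2, which is 0.75 at r = 0.5 and 0.85 at r = 0.7.
- ANCOVA variance relative to final value: 1 - r², which is 0.75 and 0.51.

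**Step 3. Power with 20 per arm, difference 6.9, S = 6.73** (two-sample noncentral t):

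| Analysis | SD, r = 0.5 | Power | SD, r = 0.7 | Power |
|---|---|---|---|---|
| Change score (= group-by-time) | 6.73 | 88.5% | 6.73 | 88.5% |
| Final value | 6.73 | 88.5% | 8.69 | 68.7% |
| ANCOVA | 5.83 | 95.4% | 6.20 | 92.9% |

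A simulation that includes the degree of freedom spent on the covariate and chance baseline imbalance gives 94.8% and 91.9% for ANCOVA, so the table is at most about one point high.

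**Step 4. Range.** With 21 per arm, S = 6.72 and r from 0.3 to 0.9, ANCOVA has 98.1% down to 91.5% power, the change score 90.1% throughout, and the final value 97.0% down to 30.6%. If 6.72 is instead the SD of the final value, power for final value, change and ANCOVA is 90.1, 78.3 and 92.5% at r = 0.3, and 90.1, 98.7 and 99.5% at r = 0.7. ANCOVA leads in each case.

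**Step 5. Unequal variances.** Let k be the week-12 SD divided by the baseline SD, with the baseline SD set to 1. The variance of change is 1 + k² - 2rk; the ANCOVA variance is k²(1 - r²). At r = 0.7:
- k = 1: 0.510 against 0.600, a 15% gain.
- k = 1.2: 0.734 against 0.760, a 3% gain.
- k = 1.4: 1.000 against 1.000, no gain.
- k below 1: a larger gain; at k = 0.8, 0.326 against 0.520, or 37%.

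**Step 6. Repeated-measures ANOVA on two ALT values.** The group-by-time term equals the change-score t-test (88.5%). The group main effect compares the means of the two visits, so it estimates 6.9/2 = 3.45.

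**The case against.** The strongest reply has four parts.

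1. **The repeated-measures sentence may not concern ALT.** Follow-up assessments are those at weeks 4, 8 and 12, and the physical activity questionnaire is taken at weeks 0, 4, 8 and 12. Repeated-measures ANOVA suits such data. This stands: a reader might infer that ALT will be tested by the diluted group main effect, but the article neither ties that ANOVA to ALT nor names that term. The halving in Step 6 is a trap to close, not a planned error.

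2. **A t-test on change does use baseline.** Both the word relief and the planning figures, which are decreases, point towards change. This also stands. A reader might infer that baseline ALT is ignored altogether; that is true only of a test on final values. The likelier comparator is the change score, against which the gain is modest.

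3. **The size rests on unstated inputs.** The SD is back-solved, r is assumed, and equal variance may fail because patients are recruited partly on abnormal liver enzymes. This stands, and Step 5 shows the effect. A reader might also infer that ALT is known to be skewed and must be logged; nothing in the article says so, and the power figures are on the raw scale.

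4. **Covariates are often left to the analysis plan.** This does not remove the point. The article chooses its comparison methods, and the change proposed is a specific replacement for them, not a request for more detail.

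**Conclusion.** The point holds as a matter of efficiency. ALT has one post-baseline value, and no named comparison method adjusts for baseline ALT. The planned tests are valid under randomisation, so the documents do not support a charge of bias.

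On the assumptions shown (20 completers per arm, SD of change about 6.7, equal variances, r of 0.5 to 0.7), ANCOVA raises power over a change score by roughly 4 to 7 points, or 3 to 6 in simulation. The gain over a final-value test is about 7 points at r = 0.5 and 24 at r = 0.7. The advantage over change narrows, and can vanish, if ALT is more variable at week 12 than at baseline. In large samples ANCOVA is not less precise than either unadjusted test; its cost is one degree of freedom. The precision is worth having, since the expected 40 completers fall short of the plan's own minimum of 42.

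**What to change.** In the Data analysis section:

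- Name as the primary analysis an ANCOVA of week-12 ALT on treatment and baseline ALT, run on the multiply imputed data that the section already provides for. Report the adjusted difference with its confidence interval.
- Fix the scale (raw or log) before unblinding.
- Use the same model for the other numerical measures taken only at weeks 0 and 12.
- Limit repeated-measures ANOVA to data collected at weeks 0, 4, 8 and 12, such as the physical activity questionnaire, and state that the group-by-time term is the one to be read.

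The cost is a change of wording. It needs no new visit, sample or patient, because baseline ALT is already collected.

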### Gut microbiota and intestinal permeability

The stool (take two samples every time) will be collected at the baseline before the intervention and the end of 12 weeks intervention for the gut microbiota analysis. The participants will be instructed to collect, store, and transport the fecal samples on proper methods. A convenient specimen collection box will be provided to all patients before the beginning of the intervention. They will be advised to take 2–3 g of fecal samples each time and then immediately store the samples into their own freezer (at least -20 °C). Afterwards, the individuals will notify the researchers to transfer the samples to a -80 °C refrigerator until analysis. For the gut microbiota assessment, total DNA will be extracted from 150 mg of fecal with the QIAamp DNA mini kit (Qiagen, Valencia, CA, USA). The purity and concentration of DNA will be detected by gel electrophoresis for sequencing and bioinformatics analysis. Raw reads will be filtered to remove adaptors and low-quality and ambiguous bases, and then paired-end reads will be added to tags by Fast Length Adjustment of Short reads program (FLASH, vl.2.11) to get the tags. The tags will be clustered into OTUs with a cutoff value of 97% using UPARSE software (v7.0.1090) and chimera sequences will be compared with the Gold database using UCHIME (v4.2.40) to detect. The sequencing data will be analyzed by QIIAME v1.8.0. In addition, the short chain fatty acid (SCFA) concentrations will be determined in the fecal supernatant using the gas chromatograph-mass spectrometer (Agilent 7890B-5977A, USA) for sample analyzing and using ChemStation software (Agilent, USA) for data handling.

The intestinal barrier function and permeability will be determined by the concentration of serum claudin-3 and LPS in plasma. As described above, the blood samples will be used to evaluate the changes of claudin-3 and LPS concentration before and after the intervention. According to the manufacturer’s instructions, serum biomarkers claudin-3 will be measured by ELISA, and the LPS will be performed through the limulus test method.

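### For overall gut community composition the plan names only estimation, unsupervised clustering and plots, with no between-arm comparison and no stated use of the paired baseline stool

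*Protocol article*

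**What the plan says.** In the protocol article, the Aim section makes the effect of LBP on the gut microbiota a secondary objective, and abundance and diversity come first in the list of secondary outcomes. Under Gut microbiota and intestinal permeability, stool is "collected at the baseline before the intervention and the end of 12 weeks intervention for the gut microbiota analysis".

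The Data analysis section gives the microbiota its own paragraph, with these steps:

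- Diversity: "The alpha and beta diversity of the gut microbiota will be estimated by MOTHUR and QIIME at the OUT level, respectively".
- Grouping: "Sample cluster will be conducted by QIIME based on UPGMA".
- Function: "KEGG and COG functions will be predicted using the PICRUSt software".
- Display: "Barplot and heatmap of different classification levels will be plotted with T package v3.4.1 and R package “gplots”, respectively".

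The paragraph ends with a general threshold: "All results are statistically significant with *P*<0.05". The paragraph before it sets the general tests. Numerical variables are summarised as means or as "medians with interquartile ranges (IQR) comparing by Student’s *t* test or the Mann-Whitney *U* test", and "Follow-up data will be compared using the repeated measures analysis of variance (ANOVA").

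**The concern.** The trial asks whether LBP shifts the gut community relative to placebo. An answer needs a contrast between arms, preferably one that removes the large stable differences between people. UPGMA builds a tree from between-sample distances. Neither treatment arm nor patient identity is an input, and the output is a grouping, not an effect estimate, interval or P value. Bar plots and heat maps are displays.

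The general tests do not close this gap for overall composition. They need one value per patient per visit, whereas beta diversity is a distance between each pair of samples. So a P<0.05 threshold is set, but no named method produces a P value for composition as a whole.

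If the community-level result were then read from a tree or heat map, a real shift could be lost among person-to-person differences, and a chance grouping could be taken for an effect. The baseline stool, which could remove much of that variation, has no stated role in comparing communities.

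**Working it through.** The plan gives no sample size, power or error rate for the microbiota, so there is no figure of its own to reproduce. The check has four parts.

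**1. Which named method can compare arms, and on what?**

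| Quantity | Form of the data | Named method that can compare arms |
|---|---|---|
| Alpha-diversity index | one value per patient per visit | t, Mann-Whitney; repeated measures ANOVA uses baseline |
| Abundance of one taxon | one value per patient per visit | the same |
| Beta diversity (composition) | distance for each pair of samples | none directly; only estimation, UPGMA and plots |

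With 50 patients, one visit gives 50 × 49 / 2 = 1,225 distances. Both visits together give 100 × 99 / 2 = 4,950. These distances share samples, so they are not independent observations for a t test.

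**2. What the baseline stool is worth.** Let r be the correlation between a patient's two visits. Relative to week 12 alone (variance 1), change from baseline has variance 2(1 − r), and regression on baseline has 1 − r². The plan gives no r. Assume a between-person SD of 1 and a within-person SD of 0.6 on a log-ratio scale:

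- r = 1 / (1 + 0.36) = 0.735
- change: 2 × (1 − 0.735) = 0.53
- regression on baseline: 1 − 0.735² = 0.46

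A taxon shift of 0.5 is then 0.5 / √1.36 = 0.43 SD at week 12, and 0.5 / √0.72 = 0.59 SD on change. Change beats week 12 alone only if r exceeds 0.5. Regression on baseline is never worse than either in this large-sample comparison.

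**3. Illustrative simulations, 25 per arm.** All effects, SDs and numbers of taxa are assumptions. Each entry is the percentage of trials with P<0.05. The UPGMA row cuts the tree into clusters and tests association with arm. That test was devised for illustration and is not in the plan.

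| Method | A: 40 taxa, 8 shifted by 0.5; SDs 1 and 0.6 | B: 60 taxa, 10 shifted by 0.5 / 1.0; SDs 1.2 and 0.6 |
|---|---|---|
| UPGMA clusters against arm | 0–0.7 | 0.3 / 1 |
| PERMANOVA, week 12 | 47 | 12 / 73 |
| PERMANOVA, within-patient change | 76–88 | 82 / 100 |
| Single-taxon tests, Bonferroni-corrected | 16–41 | not run |
| Mann-Whitney on summed abundance of the shifted taxa | not run | 53 / 98 |
| t test on change in alpha diversity | not run | 4.3 / 8.0 |

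With no shift, PERMANOVA rejected in 6.0% (week 12) and 6.7% (change) of trials under A, and in 5.3% and 4.3% under B. These are near the nominal 5%.

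**4. Reading the table.**

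- Two runs on the inputs of A gave 76% and 88% on change. The standard error for 300 trials at 88% is √(0.88 × 0.12 / 300), about 1.9 points. The gap therefore probably reflects modelling detail rather than chance, and the result should be quoted as a range.
- In B the week-12 test used Bray-Curtis distances and the change test used log-ratio distances. The step from 12% to 82% thus mixes the metric with the use of baseline. A is the cleaner contrast.
- The 53 / 98% for Mann-Whitney presumes that the shifted taxa are known beforehand. The article names no target taxa as outcomes.
- In B the alpha-diversity test stayed close to its null rate of 5.7%, so a compositional shift need not show in alpha diversity.

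**The case against.** The strongest reply is that this is an omission in a condensed article. A distance-based test and its permutation scheme are details that an analysis plan usually holds, and that plan is not shown. This lowers the weight of the point but does not remove it. The article specifies the microbiota methods down to software versions, OTU cutoff, clustering algorithm and plotting packages, and the methods it names for overall composition do not answer the stated question.

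Second, much of the outcome is covered. Abundance and alpha diversity are scalar, the named tests apply to them, and repeated measures ANOVA can use baseline. This stands. A reader might infer that the plan cannot show any LBP effect on the microbiota; the document does not support that.

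Third, no sentence makes UPGMA the comparison of arms or says that an effect will be read from clusters. The closing P<0.05 sentence suggests that tests are intended, and the clustering may already be meant as description. This also stands: the defect is that no comparison is named, not that clustering is declared to be one.

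Fourth, the named tests could be applied to a scalar derived from distances, such as each patient's baseline-to-week-12 distance or an ordination score. That is correct, but no such scalar is named.

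Fifth, the cluster test in the simulation is artificial and very conservative (0% and 0.3% rejection with no shift), so its low detection partly reflects how the tree was cut. This is fair. The contrast that matters is between week 12 and change.

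**Conclusion.** The point holds for overall community composition. The methods named for it give no between-arm estimate or P value and make no stated use of the paired baseline stool. It does not extend to alpha diversity or single-taxon abundance, which the general tests can handle.

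A reader might also infer that the tree will simply pair each person's two stools. That would apply only if both visits are clustered together, and the article does not say which samples enter the tree.

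The size of the loss cannot be taken from the document. On assumed inputs, PERMANOVA detected the shift in about 47% of trials at week 12 and in 76–88% on change. The gain rests on the assumed shift and on strong within-person correlation (r of about 0.74). Severity is low to moderate: the primary aim is hepatic injury, the microbiota outcome is secondary, and an unseen analysis plan may already name a test.

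**What to change.** In the Data analysis section, before unblinding:

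1. Name one between-arm comparison of overall composition that uses baseline. For example, compute each patient's week-12 minus baseline profile on the centred log-ratio scale and compare arms by PERMANOVA with arm labels permuted across patients.
2. Compare week-12 alpha diversity by regression on arm and baseline alpha diversity, reporting the adjusted difference with its confidence interval.
3. Say which samples enter the UPGMA tree, and label the tree, bar plots and heat maps as descriptive, with no claim of effect drawn from them.

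The cost is a few sentences and slight extra analysis in standard software; samples and sequencing are unchanged. One consequence should be stated: a patient without both stools cannot contribute a change profile, so the number of complete pairs per arm should be reported.
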